## Explorative analyses

Secondary and other outcome variables are tested as well and as far as it is promising. However, these tests are only explorative, not confirmatory, i.e. they generate new hypotheses. Further, subgroup analyses will be done with descriptive measures and explorative testing as far as interesting results are expected.

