# OBJECTIVES

*Primary Objectives:*

-Does short-term treatment (3 months) with benfotiamine in diabetic nephropathy result in a lowering of urinary excretion of β2-microglobulin and albumin?

*Secondary Objectives:*

-Does short-term treatment (3 months) with benfotiamine result in a lowering of urinary excretion of established and emerging markers of tubulointerstitial damage and inflammation, such as KIM-1, MIF, MCP-1, and C3d in patients with diabetic nephropathy (the expression of MCP-1 in the kidney and the amounts of MCP-1 in urine have, for instance, been shown to be associated with severity of tubulointerstitial disease and to predict the loss of renal function in several types of chronic kidney disease (27-32))?

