## Inclusion criteria

• Type 2 diabetes mellitus
• Age: 40-75 years
• Patients are on treatment with angiotensin converting enzyme inhibitors (ACEi) and/or angiotensin II antagonists (AIIA) in an unchanged dose for at least 3 months
• Active diabetic nephropathy as indicated by presence of microalbuminuria (30-300 mg/24 h urine) in at least two samples within 2-6 weeks in advance of inclusion in the trial
• HbA1c < 8.5%, a higher HbA1c  9.5% is acceptable if the treating physician and the patient have accepted that striving for lower values is an unreachable goal (patients with high HbA1c values are the ones that one would expect to be benefit most from treatment with benfotiamine)
• eGFR (estimated by MDRD formula) > 30 ml/min
• Males and postmenopausal females
• Written informed consent

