### Secondary study parameters/endpoints

Change in urinary excretion of (measured in 24-hour urine):

• KIM-1 (kidney injury molecule-1)
• MIF (macrophage inhibiting factor)
• MCP-1 (monocyte chemo-attractant protein-1)
• C3d
• Urinary peptidomics
• Reactive oxygen species, advanced glycation end-products (AGEs), and carbonylated albumin

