# STATISTICAL ANALYSIS

## Descriptive statistics

First, study patients will be described with their demographical and medical data. This will be done for the entire study population to describe study patients. Additionally this will be done separately for each of the two groups to investigate comparability of the groups (which might be disturbed due to drop-outs). Further, all outcome variables will be evaluated with descriptive statistical methods. For quantitative variables this includes maximum, median, mean, minimum as well as standard deviation. For qualitative variables absolute and relative frequencies will be used.

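### Section 9.3 makes testing of the fixed secondary markers depend on its being promising, which leaves the secondary objective open to selective testing

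*Protocol*

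**What the plan says.** - **Protocol, section 2 (Objectives).** The secondary objective is a direct question: does treatment "result in a lowering of urinary excretion of established and emerging markers of tubulointerstitial damage and inflammation"? Four markers are then named as examples: KIM-1, MIF, MCP-1 and C3d.
- **Protocol, section 7.1.2.** The same four markers are listed as secondary endpoints, without condition. Urinary peptidomics follows, and then "Reactive oxygen species, advanced glycation end-products (AGEs), and carbonylated albumin". Counting peptidomics as one item, the list has eight.
- **Protocol, Summary (burden, risks and benefit).** An improvement in the markers of tubulointerstitial damage and inflammation is given as the ground on which benfotiamine could go forward to larger efficacy studies.
- **Protocol, section 9.1.** "Further, all outcome variables will be evaluated with descriptive statistical methods". For quantitative variables the measures named are maximum, median, mean, minimum and standard deviation.
- **Protocol, section 9.3.** "Secondary and other outcome variables are tested as well and as far as it is promising". The next sentence limits the claim: "However, these tests are only explorative, not confirmatory, i.e. they generate new hypotheses". On subgroups: "subgroup analyses will be done with descriptive measures and explorative testing as far as interesting results are expected".

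**The concern.** Two parts of the protocol do not fit together. The objective and the endpoint list commit to a question about named markers. The analysis section makes the test of each marker conditional on a judgement, and does not say what that judgement rests on, who makes it or when.

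This is more than detail left to a statistical analysis plan. It is a stated rule, and an analysis plan that followed it could leave any listed marker untested. If the judgement were made with results in view, markers that moved favourably by chance would be tested and the others would not. The tested markers would then look better than they are.

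The markers are the mechanistic rationale of the trial and, by the Summary, part of the case for larger trials. An overstated marker effect would feed that decision.

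**Working it through.** **Inputs**
- 38 evaluable patients per group, effect size 0.65 SD, 80% power, one-sided 2.5%, 10% drop-out, 43 randomised per group (section 4.4).
- Four named markers (section 2) and eight listed secondary items (section 7.1.2).
- Assumed, because the protocol gives no figure: correlation between markers of 0 or 0.5, and no true effect on any marker.

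**1. The plan's own figure.** n = 2(1.960 + 0.842)² / 0.65² = 2 × 7.851 / 0.4225 = 37.2, rounded up to 38 per group. Power at 38 is 80.9% by the normal approximation and 79.9% by the noncentral t distribution. With drop-out, 38 / 0.90 = 42.2, rounded up to 43. The stated numbers reproduce, and none depends on the present point.

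**2. Precision of one marker comparison.** In SD units of the change score, the standard error of the group difference is √(2/38) = 0.229.

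**3. Apparent effect of the best-looking null marker.** This is the expected maximum of k standard normal variables times 0.229. With a common correlation ρ, the shared component has mean zero and does not affect the ranking, so the result is multiplied by √(1 − ρ), which is 0.707 at ρ = 0.5.

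| Markers | Independent | Correlation 0.5 |
| --- | --- | --- |
| 4 | 1.03 × 0.229 = 0.24 SD | 0.24 × 0.707 = 0.17 SD |
| 8 | 1.42 × 0.229 = 0.33 SD | 0.33 × 0.707 = 0.23 SD |

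A simulation with 200,000 replicates gives 0.236, 0.327, 0.167 and 0.231 SD, in agreement.

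**4. Against the design effect.** 0.167 / 0.65 = 26%; 0.231 / 0.65 = 36%; 0.236 / 0.65 = 36%; 0.327 / 0.65 = 50%. Choosing only the best-looking null marker would produce, on average, about a quarter to a half of the design effect by chance.

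**5. What section 9.1 covers.** It keeps every outcome variable in the descriptive results. It names summary measures only, with no between-group difference and no confidence interval. Its explicit sentence on describing the groups separately concerns patients' demographic and medical data, not outcomes.

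**The case against.** The strongest reply is that section 9.3 already calls these tests exploratory and hypothesis-generating, and that section 9.1 describes all outcomes, so no marker disappears. Much of this stands. The confirmatory claim rests on two primary outcomes under Bonferroni-Holm and is untouched. Under section 9.1 every marker stays in the descriptive results; only its test is conditional. But the exploratory label limits what may be claimed from a test. It does not correct an estimate that was singled out because it looked good, and section 9.1 promises no between-group estimate that would let a reader see the whole set.

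Stronger readings are tempting, and the protocol does not support them:

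- **That results will drive what is tested.** Section 9.3 does not say when *promising* is judged. It could be judged beforehand. Describing outcomes in 9.1 and testing them in 9.3 is an order of sections, not proof of a data-driven sequence.
- **That the secondary objective cannot be answered without selection bias.** Bias arises only if tests are chosen on results and reported selectively. The text permits that but does not require it.
- **That subgroups suffer equally.** There the wording refers to results that are *expected*, which points to prior judgement, and naming subgroups is commonly left to the analysis plan. The remark in section 4.2 that "patients with high HbA1c values are the ones that one would expect to be benefit most from treatment with benfotiamine" explains an entry criterion. It is not a stated subgroup hypothesis.
- **That familywise error measures the fault.** With independent null tests at one-sided 2.5%, the chance of at least one nominal hit is 1 − 0.975⁴ = 9.6% for four markers and 1 − 0.975⁸ = 18.3% for eight (7.8% and 12.7% at correlation 0.5). These figures would be the same if every marker were tested and reported without adjustment. They measure multiplicity, not selection, and section 9.3 sets no level for exploratory tests.

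**Conclusion.** The concern holds as an open door, not as a demonstrated bias. Section 9.3 states a conditional testing rule for endpoints that sections 2 and 7.1.2 fix without condition. With no criterion and no decision point before unblinding, the rule leaves the secondary objective open to selective testing and overstated marker effects.

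The 0.17 to 0.33 SD range is an illustration of the extreme case, in which only the single best-looking null marker is taken forward. It rests on 38 evaluable patients per group, on no true effects, on peptidomics counted as one item and on an assumed correlation of 0 or 0.5. Less severe selection would give less.

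The sample size, the primary tests and their error control do not change. The point is worth correcting because the markers bear on whether larger trials follow and the correction is nearly free.

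**What to change.** Replace the first sentence of section 9.3 with a rule that does not depend on results:

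- Every secondary endpoint in section 7.1.2 is compared between groups, preferably adjusted for its baseline value.
- Each comparison is reported with its estimate and confidence interval whatever the result, labelled exploratory, with the number of tests stated.
- Any subgroup analyses are listed before unblinding, and all others are labelled post hoc.

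Holm adjustment across the four markers, false-discovery control for peptidomics and a single prespecified HbA1c interaction are choices for the analysis plan. This correction does not depend on them.

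The cost is wording and a little more analysis. No new data and no more patients are needed.

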# ETHICAL CONSIDERATIONS

## Regulation statement

This study will be conducted according to the principles of the Declaration of Helsinki,adopted by the 18th WMA General Assembly, Helsinki, Finland, June 1964, and amended by the:
29th WMA General Assembly, Tokyo, Japan, October 1975,
35th WMA General Assembly, Venice, Italy, October 1983,
41st WMA General Assembly, Hong Kong, September 1989,
48th WMA General Assembly, Somerset West, Republic of South Africa, October 1996,
and the 52nd WMA General Assembly, Edinburgh, Scotland, October 2000.
Note of Clarification on Paragraph 29 added by the WMA General Assembly, Washington 2002
Note of Clarification on Paragraph 30 added by the WMA General Assembly, Tokyo 2004 ), and in accordance with the Medical Research Involving Human Subjects Act (WMO).

## Recruitment and consent

Subjects will be invited to participate in the study by sending letters to them, in which they will find a full explanation of the study, advantages and disadvantages of participating, and contact information of the research team members working on this study. Moreover, the letter contains contact information of independent physician, to whom subjects can address questions about the research before, during and after a study. The letter will be sent by the supervising doctor [name]. [name], internist nephrologist, and the patients will be given 2 weeks to consider their decision. The subjects are asked then to sign their written informed consent before they take part in the study. Furthermore, the patients will be requested to sign separate informed consents concerning their permission on storing small quantities of collected 24-hour urine (10 ml) and withdrawn blood (3 ml), in order to perform possible further laboratorial analyses which are not available at the current time or may turn out to be interesting (regarding diabetic nephropathy) in the frame of this research in the future. These materials will be stored in -80 ºC freezers at Isala Klinieken hospital in Zwolle. The permission of the medical ethical committee (METC) Zwolle will be requested before performing any of these possible laboratorial investigations. The general practitioners (Huisartsen) will be informed about the participation of their patients.

## Benefits and risks assessment, group relatedness

Benfotiamine, which is relatively free from adverse reactions, is going to be studied in order to prove its effect in prevention of the development of end-stage renal disease in susceptible diabetic patients. In case of positive effects on symptoms of diabetic nephropathy (albuminuria) a program on treatment of diabetic nephropathy by benfotiamine will be taken into account. Participation of diabetic nephropathy patients in this study is of great importance, and answering the questions of this clinical trial is not possible without observing and analyzing the parameters at the end of the study.

## Compensation for injury

The sponsor has a liability insurance which is in accordance with article 7, subsection 6 of the WMO.

The sponsor (also) has an insurance which is in accordance with the legal requirements in the Netherlands (Article 7 WMO and the Measure regarding Compulsory Insurance for Clinical Research in Humans of 23rd June 2003). This insurance provides cover for damage to research subjects through injury or death caused by the study.

1. € 450.000,-- (i.e. four hundred and fifty thousand Euro) for death or injury for each subject who participates in the Research;
2. € 3.500.000,-- (i.e. three million five hundred thousand Euro) for death or injury for all subjects who participate in the Research;
3. € 5.000.000,-- (i.e. five million Euro) for the total damage incurred by the organization for all damage disclosed by scientific research for the Sponsor as ‘verrichter’ in the meaning of said Act in each year of insurance coverage.

The insurance applies to the damage that becomes apparent during the study or within 4 years after the end of the study.

Subjects will be given written information about the taken out insurance when they participate in the study.

## Incentives

Participation of patients in the study is a free-will decision. Patients will not receive any financial support or priority for treatment of other diseases in the clinic during this clinical trial.

All costs that subjects need for transportation in order to attend in the clinic for the study purpose will be reimbursed completely.

# ADMINISTRATIVE ASPECTS AND PUBLICATION

## Handling and storage of data and documents

All data gathered from the subjects will be handled confidentially and anonymously.

A subject identification code list will be made to link the data to the subject in order to be able to trace data to an individual subject. This code will not be based on the patient initials and birth-date. The key to the code will be safeguarded by the investigator since the data will be kept for a longer period of time15 years. The handling of personal data will comply with the Dutch Personal Data Protection Act (in Dutch: De Wet Bescherming Persoonsgegevens, Wbp).

## Amendments

A ‘substantial amendment’ is defined as an amendment to the terms of the METC application, or to the protocol or any other supporting documentation, that is likely to affect to a significant degree:

- the safety or physical or mental integrity of the subjects of the trial;
- the scientific value of the trial;
- the conduct or management of the trial; or
- the quality or safety of any intervention used in the trial.

All substantial amendments will be notified to the METC and to the competent authority.

Non-substantial amendments will not be notified to the accredited METC and the competent authority, but will be recorded and filed by the sponsor.

## Quality control and Quality Assurance

The protocol requires that the investigators will permit trial-related monitoring, audits and reviews, and regulatory inspection(s), providing direct access to source data/documents.

Quality control will be ensured by regular visits of an independent person designated by the sponsor. All people participating in the investigation will participate before initiation of the trail to at least one common reunion where requirements for quality will be trained. The study will be conducted according to actual guidelines for GCP. All participating investigators are well trained and experienced in the investigation to be performed, the principal investigator has more than 15 years experience in conducting clinical trials.

## Annual progress report

The sponsor/investigator will submit a summary of the progress of the trial to the accredited METC once a year. Information will be provided on the date of inclusion of the first subject, numbers of subjects included and numbers of subjects that have completed the trial, serious adverse events/ serious adverse reactions, other problems, and amendments.

## End of study report

The sponsor will notify the accredited METC and the competent authority of the end of the study within a period of 90 days. The end of the study is defined as the last patient’s last visit.
In case the study is ended prematurely, the sponsor will notify the accredited METC and the competent authority within 15 days, including the reasons for the premature termination.
Within one year after the end of the study, the investigator/sponsor will submit a final study report with the results of the study, including any publications/abstracts of the study, to the accredited METC and the Competent Authority.

## Public disclosure and publication policy

This study is part of the EU-financed project PREDICTIONS with different participating parties. Before public disclosure, all knowledge generated in the project (e.g. pre-submission manuscript) will be submitted to project coordinator who will be requested to provide any recommendations for new patent application within 30 days. Where knowledge is to be protected, patent applications will be prepared by the concerned parties, according to their established practices.

In order to protect the confidential information, prior to submission for publication or presentation, the Publication Committee of PREDICTIONS shall provide each party 45 days to review any manuscript and 30 days to review any poster presentation, abstract or any other written or oral material which describes or discloses the results of the study. In addition, if one party requests in writing and demonstrates evidently that it is necessary to protect the rights of that party, the Publication Committee can withhold any publication or presentation an additional 45 days. Each party can demand to remove confidential information from a publication which could be damaging to party’s rights. The Publication Committee shall, in as far as it does not thereby compromise its scientific integrity, attempt to adapt its publication in such a way that party’s objections are met. Wörwag Pharma as manufacturer and the study medication will be named in any publication.

In case of results relevant for prophylactic or therapeutic intervention with benfotiamine in patients with diabetic nephropathy, Wörwag Pharma GmbH & Co. KG reserves the right of patent application nationally and internationally on his own behalf. Wörwag Pharma GmbH & Co. KG commits to announce the investigator(s) as inventors. The investigator(s) commit to render all statements and giving all signatures necessary for patent application towards authorities and patent offices. Wörwag Pharma GmbH & Co. KG bears all expenses in connection with patent application and grant of a patent. All rights and claims of the investigator(s) in connection with potential patents on the prophylactic of therapeutic use of benfotiamine in diabetic nephropathy are covered by the funding based on the PREDICTIONS contract. Other compensations by Wörwag Pharma are excluded.

Reference List

